**Interval training on treadmill**			
*Intensity [HR as % of* HR_peak_*]*	65-70	70-80	80-90
*Interval duration [minutes]*	3	2-2.5	1-2
*Number of intervals*	4-7	6-10	10-12
**Strength training**			
*Number of exercises*	3	3	3
*Number of sets/exercise*	3	3	3
*Number of repetitions or time/set*	Week 1: 3 repetitions	As much repetitions in 20 or 30 seconds.	As much repetitions in 20 or 30 seconds.
	Week 2–12: as much repetitions in 20 or 30 seconds.		

### Type – interval training on treadmill

The aim of the interval training is to improve the aerobic exercise capacity as it has previously been shown to increase peak oxygen uptake in healthy children and adolescents [24]. Moreover, compared with prolonged continuous training, the short intermittent nature of the exercise better simulates natural physical activities of children [25] and it is more likely to be perceived as enjoyable in a pediatric population. During the progression of the exercise training program, the intensity of the intervals will increase simultaneously with a decrease in the duration of each bout. The interval training will be performed on the treadmill since walking and running correspond closely to activities of daily living that may be impaired in patients with JDM.

### Type - strength training

The aim of the strength training program is to improve the muscle strength of proximal muscle groups, since these tend to be most affected in JDM. Along with the recommendation that strength training in youth should include large muscle groups [3], the following 3 exercises are included: squat, abdominal crunch, and push-up. To prevent muscle damage, the exercises are concentric in nature and against gravity (no additional weight lifting). A ball is implemented in some of the exercises to maintain the playfulness of the exercise.

Interval training on the treadmill and strength training will be performed in an alternating fashion during each session.

### Frequency

In order to improve aerobic exercise capacity and muscle strength in children and adolescents, a training frequency of 3-4 [24] and 2-3 [24,26] times per week, respectively, is recommended. By taking these guidelines into account, as well as the time requirement for the patient and parents to complete the session, the training frequency during phase 1 and 2 is set at 3 sessions per week and it is reduced to 2 times per week during phase 3 together with an increase in both intensity and session duration. Consequently, the total training program consists of 32 training sessions. Subjects will be instructed to perform these sessions on non-consecutive days.

### Intensity – interval training on treadmill

It is important that the intensity of the exercise training is similar in all subjects [24]. Because of the large inter-individual variability in peak heart rate (HR_peak_) among children [24], the intensity of the treadmill training in the current study will be defined by HR as percentage of HR_peak_, which will be assessed prior to training at T0 (intervention group) or T1 (control group). In this way, the standardization of the intervention is guaranteed.

Baquet et al. [24] state that training at a HR > 80% of HR_peak_ may be essential in order to improve aerobic exercise capacity in healthy children and adolescents. However, this threshold intensity is likely to be reduced for most deconditioned patiens with a chronic condition. Durstine et al. [22] suggested a training intensity with an oxygen uptake of 10-60% of peak oxygen uptake in these chronic patients, which corresponds to approximately a HR of about 66% of HR_peak_[27]. Taking these guidelines into account, exercise intensity in the current training program will begin at a HR of 65% of HR_peak_ and increase to a HR of 90% of HR_peak_ by the end of the program. Further, periods of high intensity exercise (3–1 minutes at HR of 65-90% of HR_peak_) will alternate with short periods of low intensity exercise (1 minute at a HR of 50-60% of HR_peak_).

The intensity of the intervals is ascertained in advance (see Table 1) and it is constant for intervals during a single training session. The initial gradient of the treadmill during the intervals is set at 0% for each subject. The speed will be adjusted individually in such a way that the HR during the intervals is approximately 65% of HR_peak_. This combination of gradient and speed is called level 1. In total, 24 levels are formulated in which the next level is either characterized by an increase in speed (alternately 0.6 and 0.4 km·h^-1^) or an increase in gradient of 1%.

During the intervals, subjects and parents will monitor their HR using a heart rate monitor (DKN Technology, Belgium). If HR does not fall within the predefined training range, the intensity of the next training session will be increased or decreased by 1 level so as to maintain the proper intensity.

### Intensity - strength training

For strength training in healthy children and adolescents, 1–3 sets of 6–15 repetitions are recommended [26,28]. In the current training program, each of the 3 exercises consists of 3 sets. During the first week, only 3 repetitions are prescribed per set so as to ensure the subjects develops proper strength exercise techniques [26]. Over the course of the subsequent 11 weeks, the intensity of the strength training is set by time. Squats will be performed for 30 s per set and both the abdominal crunches and push-ups will be performed for 20 s per set. All exercises have 2 possible extensions in which the exercise load becomes heavier and more challenging. An extension will be prescribed when the subject shows proper techniques and describes the exercise as light or easy.

Subjects will be given a 1 min rest period between sets according to the recommendations of Faigenbaum et al.[26]. Such a short period allows for the development of muscular endurance [29], which is highly desired in this patient group.

### Time and duration

The total time per session, which includes treadmill training, strength training, warming-up, cooling-down, and rest periods, is 40–60 minutes. Each session consists of 15–25 minutes at or above the threshold intensity, as recommended by Takken et al. [23] The program duration is set at 12 weeks according to the recommendations for exercise training in children with chronic conditions [30].

### Warming-up and cooling-down

Each exercise session starts and ends with a 5-min during low intensity walk on the treadmill at a HR of 50-60% of HR_peak_[26].

### Supervision

Each subject will receive a detailed and individualized description of the exercise program and will be asked to keep track of every completed stage. Parents will be asked to be present at each training session to provide their child with support and motivation, to ensure proper strength training techniques, as well as to assist them with the use of the treadmill and the HR monitor. Furthermore, the subjects will be asked to keep a day-to-day journal for training compliance. Every 2 weeks, a researcher or physiotherapist will conduct a home visit to observe the training session, to ensure compliance, to motivate the subject, as well as to make adjustments to the training prescription as needed.

### Randomization and blinding

Included subjects will be stratified according to age (≤ or >12 years) and gender after which they will be randomized to either the intervention or the control group. The randomization process will be performed by a person with no clinical involvement in the trial. Blocking is used to ensure close balance of the numbers in each group at any time during the trial. Randomly varying the block size (2 or 4) reserves the unpredictability of the sequence. The sequences will be concealed until interventions are assigned. The researchers performing the assessments, as well as those charged with data analyzes will be blinded to treatment allocation.

### Baseline description of groups

The baseline descriptors of the groups are age, gender, anthropometrics and disease characteristics. The anthropometrics include maturity offset (years), height (M), body mass (kg), body mass index (kg·m^-2^), and fat free mass (kg). The disease characteristics include age at diagnosis (years), disease duration at inclusion (years), disease course (monocyclic/ polycyclic/ chronic), and medication usage. These descriptors will be compared between the treatment group and the control group at T0. Maturity offset will be determined with gender-specific equations including chronological age, height, body mass, and sitting height [31]. Fat free mass will be measured with BODYSTAT® QuadScan 4000. Disease duration at inclusion will be defined as the time from diagnosis to inclusion. Disease course will be classified as monocyclic (no signs of disease activity 2 years after diagnosis), polycyclic (recurrence of active disease after a definite remission (>6 months), followed by one or more flares), or chronic (persistent disease activity >2 years after diagnosis)[32].

### Study outcomes

#### Efficacy

The primary and secondary efficacy outcome measures along with the tools for these assessments are described below and in Table2.

**Table 2 T2:** The primary and secondary study outcomes and the accompanying measurement tools used

	**Items**	**Range**	**+/−**
**Aerobic exercise capacity***(Maximal exercise test on treadmill)*			
VO_2peak_ [l·min^-1^]	na	>0	+
VO_2peak/kg_ [ml·kg^-1^·min^-1^] ^1^	na	>0	+
O_2_ pulse [ml·beat^-1^]	na	>0	+
Endurance time [min]	na	>0	+
VO_2VAT_ [l·min^-1^]	na	>0	+
VO_2VAT/kg_ [ml·kg^-1^·min^-1^]	na	>0	+
**Isometric muscle strength***(Hand-held dynamometry – Break method)*			
Maximal force right knee extensors [N]	na	>0	+
Maximal force left knee extensors [N]	na	>0	+
Maximal force right hip flexors [N]	na	>0	+
Maximal force left hip flexors [N]	na	>0	+
**Perception of fatigue***(PedsQL Multidimensional Fatigue Scale – patient form)*			
Total score	18	0-100	+
Subscale *General Fatigue* score	6	0-100	+
Subscale *Sleep/Rest Fatigue* score	6	0-100	+
Subscale *Cognitive Fatigue* score	6	0-100	+
**Muscle soreness***(10-cm Visual Analogue Scale muscle soreness)*			
Visual Analogue Scale muscle soreness [cm]	na	0-10	-
**Muscle function***(BOT-2 Subscale 8 – Strength)*			
Total score	5	0-42	+
Item *Distance standing long jump* [m]	na	>0	+
Item *Amount of sit-ups in 30 s*	na	≥0	+
Item *Amount of push-ups in 30 s*	na	≥0	+
Item *Time wall sit* [s]	na	0-60	+
Item *Time V-up* [s]	na	0-60	+
**Muscle function***(Childhood Myositis Assessment Scale)*			
Total score	14	0-52	+
**Functional sub maximal aerobic exercise capacity***(6-Minute Walk Test)*			
Distance [m]	na	>0	+
**Physical activity enjoyment***(Physical Activity Enjoyment Scale)*			
Total score	17	17-119	+
**Quality of life***(PedsQL Generic Core Scale – patient form)*			
Total score	23	0-100	+
Subscale *Physical Functioning* score	8	0-100	+
Subscale *Emotional Functioning* score	5	0-100	+
Subscale *Social Functional* score	5	0-100	+
Subscale *School Functioning* score	5	0-100	+
**Functional ability***(Childhood Health Assessment Questionnaire 30 + 8)*			
Subscale *Dressing* score	4	0-3	-
Subscale *Arising* score	2	0-3	-
Subscale *Eating* score	3	0-3	-
Subscale *Walking* score	2	0-3	-
Subscale *Hygiene* score	5	0-3	-
Subscale *Reach* score	4	0-3	-
Subscale *Grip* score	5	0-3	-
Subscale *Activities* score	5	0-3	-
Subscale *School/Extracurricular* score	8	0-3	-
Disability score [%]	38	0-100	-
Visual Analogue Scale pain [cm]	na	0-10	-
Visual Analogue Scale global disease severity [cm]	na	0-10	-
**Physical activity***(Actical accelerometer for 7 days)*			
	na	>0	+
**Physical activity***(Activity journal for 2 weekdays + 1 Saturday)*			
Time inactive [%]	na	0-100	-
Time light active [%]	na	0-100	−/+
Time moderate active [%]	na	0-100	−/+
Time vigorous active [%]	na	0-100	+

Abbreviation: na: not applicable.

^1^ the primary outcome measure on which power calculation was performed.

+: an increase in value denotes an improvement -: a decrease in value denotes an improvement.

### Primary study outcomes

*Aerobic exercise capacity* will be measured with a treadmill-based (RAM, Accuramed BVBA, Lummen, Belgium) incremental maximal exercise test according the protocol set out by the German Society for Pediatric Cardiology [33]. Briefly, the test starts at a speed of 2 km·h^-1^ with a 0% grade; the speed increases by 0.5 km·h^-1^ and the grade by 3%, up to a maximum of 21%, every 90 s. The test is terminated upon voluntary exhaustion, despite strong verbal encouragement.

Throughout the test, the subject will wear a facemask (Hans Rudolph Inc, Kansas City, MO) connected to a gas analysis system (ZAN 600, Accuramed BVBA, Lummen, Belgium), which will allow for a sample of expired gases to pass to a flowmeter, an oxygen analyzer, and a carbon dioxide analyzer. Volume calibration and gas analysis calibration will be performed before each testing session. The flow meter and gas analyzers are connected to a computer that calculate breath-by-breath minute ventilation (VE), oxygen uptake (VO_2_), carbon dioxide output (VCO_2_), and the respiratory exchange ratio (RER = VCO_2_/VO_2_) using conventional equations. HR will be measured continuously via a 12-lead electrocardiogram (CardioPerfect, IT medical, the Netherlands). The test will be deemed maximal when the HR is >180 beats·min^-1^ and/or the RER >1.0.

The outcome measures related to aerobic exercise capacity that will be assessed include: VO_2peak_ [l·min^-1^]: the average volume of the absolute oxygen uptake during the last 30-s period of the test; VO_2peak/kg_ [ml·kg^-1^·min^-1^]: the absolute VO_2peak_ divided by body mass. This variable was used for the power calculation; VO_2VAT_ [l·min^-1^]: the absolute VO_2_ eliciting the ventilatory anaerobic threshold (VAT). The VAT will be determined as defined by an increase in both the ventilatory equivalent of oxygen (=VE/VO_2_) and end-tidal pressure of oxygen with no concurrent increase in the ventilatory equivalent of carbon dioxide (=VE/VCO_2_); VO_2VAT/kg_ [ml·kg^-1^·min^-1^]: the absolute VO_2VAT_ divided by body mass; O_2_ pulse [ml·beat^-1^]; and endurance time [min]: the time from the start to the end of the protocol.

*Isometric muscle strength* of the proximal muscle groups in the lower extremities will be measured on both the right and left sides with a calibrated CITEC hand-held dynamometer (C.I.T. Technics, Groningen, the Netherlands). Both the extensors of the knee joint and the flexors of the hip joint will be assessed with 3 consecutive measurements according to the ‘break method’, wherein the examiner gradually overcomes the muscle force and stops at the moment the extremity gives way [34]. The highest value of the 3 repetitions will be recorded. All within-subject tests will be performed by the same assessor using the same hand-held dynamometer to prevent inter-observer and inter-instrument bias [34].

*Perception of fatigue* will be measured with the Dutch translated PedsQL Multidimensional Fatigue Scale. This scale, designed to measure fatigue in pediatric patients, reflects 3 subscales: general fatigue, sleep/rest fatigue, and cognitive fatigue [35-37].

### Secondary outcome measures

*Muscle soreness* will be measured using a 10-cm Visual Analogue Scale (VAS). *Muscle function* will be assessed via Subscale 8 (Strength) of the Bruininks-Osteretsky Test of Motor Proficiency, Second Edition (BOT-2), which include 5 items that are related to the strength training program of the subjects [38]. The Childhood Myositis Assessment Scale (CMAS) is specially designed to assess the functional consequences of proximal muscle strength and endurance, and will also be utilized as a marker of *muscle function* in our subjects [39]. *Functional sub maximal aerobic exercise capacity* will be assessed by examining walking distance at the 6-min walk test (6MWT) [40]. This will be followed by an assessment of *physical activity enjoyment* using the Physical Activity Enjoyment Scale (PACES) [41]. *Quality of life* will be measured with the patient form of the Dutch translated PedsQL Generic Core Scale [36,42,43]. *Functional ability* will be measured with the Childhood Health Assessment Questionnaire (CHAQ), a disease specific questionnaire that measures the grade of disability in performing activities of daily living as observed by the parents [44-46]. The VAS discomfort items of the CHAQ will be filled in by the subjects. Finally, habitual levels of *physical activity* will be monitored via accelerometry (Actical) [47] and a Bouchard activity journal [48,49] over a 7 day period.

### Power calculation

A power calculation was performed based on previously published data relating to one of the primary outcome measures: VO_2peak/kg_. The mean ± standard deviation VO_2peak/kg_ of patients with JDM (in remission) is 33 ± 8 ml·kg^-1^·min^-1^[13]. The aim of this training intervention is to improve VO_2peak/kg_ by at least 22%, which is the weighted mean improvement in exercise training studies in adults with inflammatory myositis [17]. Given an 80% probability of detecting a treatment effect, with significance set at 0.05 (two-tailed), the required number of total subjects is 22; 11 in each of the 2 groups. Upon factoring in a 20% (*n* = 5) chance of missing observations and/or drop-outs, the total sample size increase to 27 patients. For simplicity in the randomization process, we want to include 30 patients.

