## Methods/design

### Study design

The current study is a multi-center (4 sites) randomized controlled trial, with the control group also entering the training arm directly following completion of the initial protocol. After randomization (1:1), subjects in both groups will perform a test battery of exercise tests, questionnaires, and other measurements (see study outcomes) (T0 measurement). Thereafter, subjects in the intervention group will receive an exercise training regimen, while the subjects in the control group will continue to receive standard care over a 12-week period. Subsequently, subjects in both groups will repeat the battery of tests from T0 (T1 measurement). Subjects in the intervention group will then receive individual advice based on their T1 results and educated on the physical activity guidelines for children [20] in order to help maintain fitness levels following the intervention. Subjects in the control group will enroll in the exercise training program. Following this 12-week period, subjects in both groups will repeat the battery of tests from T0 and T1 (T2 measurement) and the subjects in the control group will receive individual feedback in the same manner as the intervention group at T1. After 12 weeks, the subjects in the control group will repeat the battery of tests from T0, T1, and T2 (T3 measurement). See Figure1 for a flow diagram of the study design.

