#### Intervention group Vs control group

To examine the efficacy of the intervention, the outcome measures of the intervention group and control group will be compared at each of time points T0 and T1 using mixed linear regression analysis with group (intervention/control) as independent variable and the outcome measures (see Table2) as separate dependent variables.

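### On the plan's own inputs, 11 per group gives about 53% power rather than 80%, and enrolling 30 does not restore it

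*Protocol article*

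**What the plan says.** The Power calculation section of the protocol article uses one primary outcome, VO2peak/kg. It states that the value "of patients with JDM (in remission) is 33 ± 8" ml/kg/min. The aim is to raise it "by at least 22%, which is the weighted mean improvement in exercise training studies in adults with inflammatory myositis". The error rates are given as "Given an 80% probability of detecting a treatment effect" and a two-tailed level of 0.05. From these it concludes that "the required number of total subjects is 22; 11 in each of the 2 groups". A 20% allowance for loss takes the total to 27, and enrolment is set at 30 to simplify randomization.

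Allocation is 1:1 (Study design). Under Intervention group Vs control group, the outcomes of the two arms "will be compared at each of time points T0 and T1 using mixed linear regression analysis with group (intervention/control) as independent variable". Group is the only independent variable named. The article gives no T0–T1 correlation, SD of change or baseline-adjusted SD.

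**The concern.** The section prints every input that a two-group calculation needs, so its result can be checked. A standardized effect of about 0.9 with 80% power at a two-sided 5% level calls for about 20 patients per arm. Eleven is little more than half of that.

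VO2peak/kg is the only outcome on which power was calculated (footnote to Table 2). If the 80% is wrong, the trial's chance of showing the effect it was designed around is much lower than readers are told. The article describes the trial as the first randomized one of exercise training in this disease, so a non-significant result set against a claimed 80% could be given more weight as evidence of no benefit than it deserves.

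**Working it through.** **Inputs (Power calculation; allocation from Study design).** Mean 33, SD 8, improvement 22%, two-sided α = 0.05, power 80%, 1:1 allocation.

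**Effect size.** δ = 0.22 × 33 = 7.26 ml/kg/min; d = 7.26 / 8 = 0.9075.

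**Attempt to reproduce 11 per group.**

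- Normal approximation: n per group = 2 × (1.96 + 0.8416)² / 0.9075² = 19.06, so 20 per group (40 in total).
- Two-sample t-test (noncentral t): 20.07 per group. Twenty per group gives 79.9%, so a strict 80% needs 21 per group (42 in total).

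Neither gives 11.

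**Power at the relevant sizes.** The t-test has 2n − 2 degrees of freedom and noncentrality d × √(n/2).

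| n per group | Situation | Noncentrality | Power (t) | Power (normal) |
|---|---|---|---|---|
| 11 | stated requirement | 2.13 | 52.6% | 56.7% |
| 12 | 30 enrolled, 20% lost (30 × 0.8 = 24) | 2.22 | 56.6% | 60.4% |
| 15 | 30 enrolled, none lost | 2.49 | 67.0% | 70.0% |
| 20 | | 2.87 | 79.9% | 81.9% |
| 21 | | 2.94 | 81.8% | 83.7% |

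**Effect detectable with 80% power (t-test, SD 8).**

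- 11 per group: 1.256 × 8 = 10.0 ml/kg/min, 30% of 33.
- 12 per group: 9.6 ml/kg/min, 29%.
- 15 per group: 8.5 ml/kg/min, 26%.

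**Could another reading of the same inputs give 11?**

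- *Rounding.* The most favourable unrounded values (mean 33.5, SD 7.5, 22.5%) give 61% at 11 per group and 76% at 15.
- *One-sided 5% test.* 16 per group are needed; power at 11 is 66% (t) to 69% (normal).
- *One-sample or paired test with SD 8.* n = 7.849 / 0.8236 = 9.5 (normal) or 11.6 (t), with 77% power at 11 and 82% at 12. This is the only calculation from the printed inputs that comes near 11. It tests change within one group and cannot justify 11 in each of two arms. That it was the formula used is a conjecture, since no test is named.

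**What would have to be true for 80%.** At 11 per group the SD would have to be about 5.8 instead of 8. Expressed as a T0–T1 correlation r, with residual SD 8√(1 − r²) for a T0-adjusted comparison and 8√(2(1 − r)) for change scores:

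| n per group | r needed, T0-adjusted | r needed, change score |
|---|---|---|
| 11 | 0.69 | 0.74 |
| 12 | 0.65 | 0.71 |
| 15 | 0.52 | 0.63 |

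**Loss allowance.** 20% of 22 is 4.4; rounding up to 5 gives 27. Dividing instead gives 22 / 0.8 = 27.5. The difference is immaterial, because 30 × 0.8 = 24 exceeds 22. The error lies in the 22.

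**The case against.** The strongest reply is that the planned analysis need not be an unadjusted comparison at T1. The article calls for mixed linear regression on outcomes measured at T0 and T1, and such a model can draw on T0. With T0 adjustment and r = 0.7, power would be 81% at 11 per group. A condensed article may also leave out a correlation that the full protocol used.

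Part of this stands. The article's wording on the mixed model is not conclusive, and 80% is attainable if the correlation is high enough. So the finding is limited to the inputs as printed. It does not rescue the paragraph, which offers a cross-sectional SD of 8 as its only measure of variability, while the analysis section names only group and compares the arms at each time point. The printed result contradicts the printed inputs, so this is more than an omitted detail.

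Two further points are fair. Results are to be reported with 95% confidence intervals, which would show the imprecision and lessen the risk of misreading a null result. And the chance of missing the target depends on how many patients are evaluable: in the unadjusted comparison it is 47% at 11 per group, 43% at 12 and 33% at 15. None of these is the 20% that the plan implies.

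**Conclusion.** The concern holds. For a two-group comparison on the stated mean, SD, effect, level and power, the requirement is 40 to 42 evaluable patients, not 22. Allowing for 20% loss, that means enrolling 50 to 53 (40 / 0.8 = 50; 42 / 0.8 = 52.5). Power is 52.6% at the stated 22. At the planned 30 it is between 56.6% (20% lost) and 67.0% (none lost).

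This rests on SD 8 applying to the comparison, with no gain from T0. It also rests on the whole 22% being the between-group difference. The 22% is an improvement reported in training studies, so using it this way assumes that controls do not change over the 12 weeks, which the article does not say. Any improvement in controls would lower power further.

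**What to change.** Keep the enrolment at 30 and rewrite the Power calculation paragraph in one of two ways.

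1. **Unadjusted T1 comparison.** State that power for a difference of 7.26 ml/kg/min with SD 8 is about 57% with 24 evaluable patients and 67% with 30.
2. **T0-adjusted comparison.** Name T0 as a covariate in the between-group analysis, state the assumed T0–T1 correlation and its source, and give the resulting power. At 12 per group this is about 69%, 76%, 84% and 94% for r = 0.5, 0.6, 0.7 and 0.8.

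If the original calculation did use a correlation or a smaller SD, print it together with the test. In either case, state that no change in controls is assumed.

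The cost is one reworded paragraph and, under option 2, a sentence in the analysis section. No extra patients are needed. Under option 1, or under option 2 with a correlation below about 0.65 at 12 per group, the stated power will fall below 80%.
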